## ABSTRACT

Background: For patients, healthcare professionals and policy makers to make informed choices about healthcare they must have information about the effects of interventions that is valid and understandable. The manner in which this information is presented affects how it is understood and subsequent decisions. The Health Information Project: Presentation Online (HIPPO) is designed to improve communication of information about the effects of healthcare based on randomized trials of alternative ways of presenting this evidence. Expected utility theory suggests that people making rational decisions should choose the option with the highest expected utility. The utility of outcomes, such as different health states, is usually expressed as being between zero and one (e.g. with death having a value of zero and a full healthy life having a value of one). Expected utility theory has been questioned for a number of reasons, including problems with how utilities are measured and observations that people often do not, in fact, choose to maximize their utilities.

Objective: The primary objective of this study is to determine which ways of presenting information about the reduction in risk of cardiovascular disease (CVD) result in decisions that are most consistent with what individuals considering starting statins for the primary prevention of CVD would be expected to decide based on their expected utilities.

Methods: The study is an Internet-based randomized trial in which participants will be randomized to one of six ways of presenting information about CVD risk reduction. Participants will be recruited through invitations to participate by email, links to the study website from Web pages that provide health information, Internet surfers who come across the HIPPO Website, being approached in public areas, Internet discussion groups of general practitioners.

Conclusions: The results of this study will help to inform decisions about how best to communicate the benefits of statins to healthcare professionals (general practitioners), individual patients and the general public.

## BACKGROUND

For patients, healthcare professionals and policy makers to make informed choices about healthcare they must have information about the effects of interventions that is valid and understandable. The manner in which this information is presented affects how it is understood and subsequent decisions.1,2  The objective of the Health Information Project: Presentation Online (HIPPO) is to improve communication of information about the effects of healthcare based on randomized trials of alternative ways of presenting this evidence.

This is the first HIPPO trial. Information about the effects of drugs used to decrease cholesterol blood levels was chosen for this study because it is a common problem and high quality evidence is available on the effects of cholesterol-lowering drugs (statins).3 The results of this study will help to inform decisions about how best to communicate the benefits of statins to healthcare professionals (general practitioners), individual patients and the general public.

This study is also a pilot study intended to test the methods that we will use in future HIPPO studies. We have therefore selected comparisons for which there exists prior research evidence. Two systematic reviews have concluded that the use of the relative risk reduction (RRR) to express the relationship between two probabilities results in individuals having a larger estimate of that relationship and being more likely to decide to treat compared with the use of an absolute risk reduction (ARR) or number needed to treat (NNT).1,2 None of the studies included in these reviews has investigated the relationship between the summary statistic that is used and the extent to which decisions are congruent with “expected utilities”.

Expected utility (or “expected value”) can be defined as follows: Under uncertainty where there is a p% chance of an outcome (X), say having angina or a heart attack, the expected utility is equal to pּUx + (1-p)ּUnot x where Ux represents the desirability (utility value) of the outcome and Unot x is the desirability of the alternative outcome (good health). If there is a p% chance of X and a q% chance of another outcome (Y), then the expected value is equal to [pּUx + (1-p)ּUnot x + qּUy + (1-q)ּUnot y]. Expected utility theory suggests that people making rational decisions should choose the option with the highest expected utility.4 The utility of outcomes, such as different health states, is usually expressed as being between zero and one (e.g. with death having a value of zero and a fully healthy life having a value of one, although some people consider some health states to be worse than death).

Expected utility theory has been questioned for a number of reasons, including problems with how utilities are measured and observations that people often do not, in fact, choose to maximize their utilities.5-9 Nonetheless, it can still be argued that as the expected utility for a decision, such as to take statins, increases one would expect that, on average, increasing proportions of people would choose to take the pills, if they are well informed. This argument does not depend on every individual choosing to maximize her utilities. Some people may make decisions based on other factors and it is difficult to accurately measure people’s utilities. Nonetheless, one would expect some degree of correlation between the expected utility of deciding to do something, such as taking pills, and the proportion of people who decide take the pills. The assumption underlying this study is that ways of presenting information about the effects of healthcare that result in decisions that are most consistent with individuals’ subjective expected utilities are best.

## OBJECTIVES

The primary objective of this study is to determine which of the following ways of presenting information about the reduction in risk of cardiovascular disease (CVD) results in decisions that are most consistent with what individuals considering starting statins for the primary prevention of CVD would be expected to decide based on their expected utilities:

1. RRR - Among those who take the pills there will be a 33% reduced risk of heart disease during the next 10 years.
2. ARR - Among those who take the pills, there will be a 2% absolute reduction in the risk of getting heart disease during the next ten years.
3. NNT – Among 50 people that take the pills for the next ten years there will be one additional person who will not get heart disease during that time.
4. Event rates - Among those who take the pills the risk of getting heart disease during the next ten years will be reduced from 6% to 4%.
5. TNT (tablets needed to be taken)10 – Among 50 people that take the pills for the next ten years, they will swallow a total of 182,500 pills and there will be one additional person who will not get heart disease during that time.
6. Whole numbers11 - Among 100 people who do not take the pills, 94 will not get heart disease and six will get heart disease during the next 10 years. It is not possible to say whether you would be one of the 94 or one of the six. Among 100 people who take the pills, the number who will not get heart disease in the next ten years will increase from 94 to 96 and the number who will get heart disease during the next 10 years, will decrease from 6 to 4.. Again, it is not possible to say whether you would be one of the 96 or one of the four.

Additional questions that this study will address are:

1. What is the effect of these different ways of presenting information about CVD risk reduction on understanding, confidence and satisfaction?
2. Which of the following two ways of eliciting the relative importance of the consequences of starting statins for the primary prevention of CVD gives “expected utilities” that are most congruent with what individuals decide?

- Visual analog scales (VAS’s)
- Likert-type rating scales (LTRS)

1. Are answers to the primary question and the two questions above consistent across patients (the general public) and general practitioners (GP’s)?
2. Are answers to the first three questions consistent across different countries (Norway, USA, Canada and Germany)?

## METHODS

### Study design

The study is a Web-based randomized trial in which participants will be randomized to one of six ways of presenting information about CVD risk reduction listed above. The relative importance of the consequences of starting statins will be elicited in two ways (VAS’s and LTRS’s) for all of the participants. The order in which this is done will be randomized.

A printout of the Webpages that will be used is attached [Available as a supporting PowerPoint file, Figure S3.1 Facimile HIPPO Webpages for protocol]. Upon logging into the study Website, participants will be given information about the study and asked to give informed consent to participate. They will be presented with a brief scenario in which they are asked to imagine that they have elevated cholesterol and are given the option of taking pills that lower cholesterol (statins). The relative importance of CVD risk reduction, taking pills and costs will be elicited using VAS’s and LTRS’s. They will then be presented with information about the effect of statins on the risk of heart disease, using one of the presentations listed above, the need to take a pill each day and the out-of-pocket costs; and asked whether they would decide to take the pills or not. Baseline risk will then be altered in the direction that shifts the expected utilities towards the opposite decision; i.e. the baseline risk will be increased for respondents who decide not to take the pills and decreased for those who decide to take the pills. Participants will then be asked what they would decide again. After this they will be asked questions about their decision and about themselves and, finally, they will be asked which of the six ways of presenting CVD risk reduction they would prefer.

### Inclusion criteria

To be included in the trial participants must be > 18 years old and literate in one of the following languages English, French, German, Norwegian.

### Recruitment

Participants will be recruited in the following ways:

- Invitations to participate will be sent to individuals by email in the US. The email addresses will be obtained through a vendor who has enlisted opt-in respondents for issues regarding health.
- Patients at a participating research facility will be given the opportunity to participate.
- Three additional means of recruiting participants will be used to assess the potential to recruit participants without sending out invitations by email and to compare the extent to which there are differences in results between participants recruited in these different ways:
  - Links to the study Website will be added to various Web pages that provide health information.
  - Internet surfers who come across the HIPPO Website will be invited to participate.
  - People will be approached in public areas, such as a shopping mall, and invited to participate using a computer that will be provided and with assistance, if it is needed.
- GPs will be contacted through Internet discussion groups or by email and invited to participate.

Potential participants will be offered options to participate in a lottery for a $100 gift certificate and to receive a report of the results of the study.

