### Allocation

Allocation to one of the six presentations will be determined by block-randomization. We have created a sequence of 600 presentation assignments by generating 100 blocks of the 6 presentations using [http://www.randomization.com](http://www.randomization.com/) (Randomization plan created on 17 April 2002, 16:03:41. To reproduce this plan use the seed 11049). This sequence will be looped and repeated until an adequate sample size is achieved.

The order in which we elicit the relative importance of the consequences of starting statins, VAS’s versus LTRS’s) will also be allocated by block-randomization.

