### Analysis

We have the following variables:

UCVD = utility of having heart disease; i.e. 1 – how difficult it would be to have cardiovascular (“heart”) disease on a scale from 0 to 1; 1 equals the most difficult

UPill = utility of having to take a pill each day; i.e 1 – how difficult it would be to have to take a pill each day on a scale from 0 to 1; 1 equals the most difficult

UCost = utility of not having to pay for pills; i.e. 1 – how difficult it would be to have to pay an additional amount of money each month for equivalent to the out-of-pocket cost of taking a statin on a scale from 0 to 1; 1 equals the most difficult

PP = probability of having heart disease with taking pills

PN = probability of having heart disease without taking pills

Using these variables we can calculate the expected utility (EU) for a decision to take pills:

EU(taking pills) = PPּUCVD + (1 - PP)ּ(1-UCVD) – (1-UPill) – (1-UCost)

Operationally this transforms to:

EU(taking pills) = PPּ(1-VAS_hrt) + (1 - PP)ּ(VAS_hrt) – (VAS_pill) – (VAS_cost)

or not to take pills:

EU(not taking pills) = PNּUCVD + (1 - PN) ּ (1-UCVD)

Operationally this transforms to:

EU(not taking pills )= PNּ(1-VAS_hrt) + (1 - PN)ּ(VAS_hrt)

and the difference between these (A):
A = EU(taking pills) – EU(not taking pills)

The difference in expected utilities can range from positive values (in favour of taking pills) to negative values (in favour of not taking pills).

If G is used to represent the presentation group to which a participant is randomised and D represents the decision to take pills or not, then the relationship between D and A can be modelled as follows:

(Eq 1)          logit(D) = 0 + 1A

To examine the relationship between the model of what participants might be expected to decide based on the expected utilities of the two options (Eq 1) with how the information was presented, Eq 1 will be fit for each group G. We will then compare the fit between different groups by comparing the R2 between the different groups.

Using a maximum-likelihood model will allow us to adjust for other factors (age, gender, profession) in a natural way. This allows us to test for differences in professional background (scientists or engineers vs GPs or other health professionals vs others), and differences across countries (Canada vs Germany vs Norway vs USA). To the extent that any of these factors are confounders, adjusting for these factors would improve the precision of our model.

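### The country comparison can be confounded by recruitment route: the opt-in e-mail panel is described for the US alone, and route is not among the named adjustment factors.

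*Protocol*

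**What the plan says.** All references are to the protocol.

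- **Objectives**, last additional question: "Are answers to the first three questions consistent across different countries (Norway, USA, Canada and Germany". The questions meant concern the best presentation, the effects on understanding, confidence and satisfaction, and the choice between VAS and Likert-type scales.
- **Recruitment**: "Invitations to participate will be sent to individuals by email in the US", and "The email addresses will be obtained through a vendor who has enlisted opt-in respondents for issues regarding health". The remaining routes (patients at a research facility, web links, surfers, public areas) carry no country. For GPs: "GPs will be contacted through Internet discussion groups or by email and invited to participate", again without a country.
- **Recruitment**, on the reason for using three further routes: "to compare the extent to which there are differences in results between participants recruited in these different ways".
- **Analysis**: "Using a maximum-likelihood model will allow us to adjust for other factors (age, gender, profession) in a natural way". The same paragraph says that this permits tests of "differences across countries (Canada vs Germany vs Norway vs USA", and it mentions confounding when it discusses adjustment.
- **Allocation**: "Allocation to one of the six presentations will be determined by block-randomization", from one repeated list in blocks of six. No stratification by country or route is stated.

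**The concern.** Country is not randomised, so a comparison of countries is only as good as the similarity of the people compared. One route, an opt-in panel of people enlisted for health issues, is described for one of the four countries. The protocol treats route as something that may change results, but route appears neither in the adjustment set for the country test nor in a stratification, nor is the comparison restricted to shared routes.

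Route could plausibly act on the quantity being compared. The Sample size section expects a larger R2 where risk information is better understood. Members of a health panel may understand such information differently from people approached in a shopping mall and helped at a computer. Age, gender and profession do not capture that difference.

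At stake is the interpretation of one secondary objective: a US difference could be read as a country effect when it arises from the way people were recruited.

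**Working it through.** **1. The protocol's own scale.** The Sample size section compares correlations on the Fisher Z scale with q = Z1 - Z2. Its table follows from

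n per group = 2 × ((z for alpha + z for power) / q)² + 3.

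For q = 0.30, two-sided alpha 0.05 and power 0.80: 2 × ((1.960 + 0.842) / 0.30)² + 3 = 177.4, against 177 in the table. All 12 entries reproduce in this way. The table is not in dispute; it supplies the scale used below.

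**2. Two kinds of route effect.**

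- *A shift in overall fit, common to all presentations.* Take R = 0.62 in the panel and 0.40 in other routes, a pair that the protocol gives as a medium effect: atanh(0.62) - atanh(0.40) = 0.725 - 0.424 = 0.30. If the panel supplied 50% or 80% of US participants and none elsewhere (assumed), overall US fit would exceed that of the other countries by about 0.5 × 0.30 = 0.15 or 0.8 × 0.30 = 0.24. Because the shift is the same under every presentation, the contrasts between presentations within the US do not change. A plain test of overall country differences would be distorted; the answer about which presentation is best would not.
- *A route effect that changes the contrast between presentations or between elicitation methods.* Only this kind biases the consistency question.

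**3. Size of the second kind, under assumptions.** Assumed, and not in the protocol: a presentation contrast of q_v in the panel and 0 in all other routes, no true country effect, no panel outside the US, and approximately linear mixing on the Z scale. Then

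false country difference = (panel share of the US sample) × q_v.

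Each Z has variance 1/(n - 3). The difference between two countries in a contrast of two presentations involves four of them, so its standard error is √(4/(n - 3)): 0.203 for n = 100 and 0.152 for n = 177 per presentation group per country. The first n is the pilot's minimum per group and the second is the table entry above. Both serve only as illustrations, because the main study's size is not yet set.

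| q_v | Panel share of US sample | False difference | Rejection at nominal 5%, n = 100 | Rejection at nominal 5%, n = 177 |
| --- | --- | --- | --- | --- |
| 0.30 | 25% | 0.075 | 6.6% | 7.8% |
| 0.30 | 50% | 0.15 | 11.4% | 16.7% |
| 0.30 | 75% | 0.225 | 19.8% | 31.7% |
| 0.30 | 100% | 0.30 | 31.5% | 50.7% |
| 0.10 | 25% | 0.025 | 5.2% | 5.3% |
| 0.10 | 50% | 0.05 | 5.7% | 6.3% |
| 0.10 | 75% | 0.075 | 6.6% | 7.8% |
| 0.10 | 100% | 0.10 | 7.8% | 10.1% |

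With q_v = 0 the false difference is zero and rejection stays at 5%. Where q_v is not zero, a larger study makes a false finding more likely.

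**4. What is not touched.** Presentation is randomised, so the primary comparison of presentations is not confounded by route. The pilot recruits only in the USA and, by the Secondary comparisons section, makes no country comparison.

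**The case against.** The case against has four parts.

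- *The text says less than it may seem to.* A reader might infer that most US members of the public come from the panel, or that no other country uses such a panel. The protocol supports neither. It gives no shares. Naming the US alone does not amount to excluding other countries, and the Abstract mentions e-mail invitations without a country limit. GPs are reached by routes with no country attached, so nothing shows a US-only route among them. This stands, and it is why the size can be given only as a range.
- *A difference in overall fit does not make the answers inconsistent.* A reader might take the q = 0.15 to 0.24 in step 2 as the bias on the consistency question. It is not, for the reason given there. This stands too.
- *Covariates for a secondary analysis belong in the statistical analysis plan.* The wording on adjustment is permissive, and the protocol says that the pilot will help to settle the analysis. This stands in part: a later plan could close the gap. But the protocol does not leave adjustment open. It names a set, mentions confounding, and omits a factor that its own Recruitment section singles out. The pilot cannot settle the matter, since it has one country.
- *Dropping the panel is expensive.* If the panel supplied 50% to 80% of US participants, excluding it from the main country comparison would discard that share of the US sample. This stands, and it argues against exclusion as the main analysis.

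**Conclusion.** The concern holds as a limited point about a secondary objective. As written, the country test can be confounded by recruitment route, a factor that the protocol itself flags and then leaves out of its named adjustment set.

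The direction and size are unknown. Under the assumptions in step 3 with q_v = 0.30, the false country difference runs from about q = 0.075 to 0.30 as the panel share goes from 25% to 100%. With q_v = 0.10 the effect on the test is slight. If route does not modify the contrasts, the consistency question is unbiased and only a test of overall country differences is exposed.

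A reader might go further and conclude that the comparison of presentations is itself compromised, or that a US difference must be a panel artefact. The documents support neither: allocation to presentation is random, and the mixing of route with country may be only partial, because other routes may also run in the US.

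**What to change.** 1. In the Analysis section, add recruitment route to the named adjustment factors for the country comparison, with terms for route by A and route by presentation. Because a route main effect can explain decisions directly and so change R2, the same aim is better met, where R2 is the measure, by fitting Eq 1 within route strata. The compared R2 then still reflects A alone. Treat the comparison of VAS with Likert-type scales in the same way.
2. Keep all participants in the main country comparison.
3. Repeat it, as a sensitivity analysis, among participants from routes used in more than one country, without the US vendor panel. Attribute a US difference to country only if it persists there.
4. State in the Recruitment section which routes run in which countries. Without this the shared routes cannot be identified. If the US sample came wholly from the panel and no other country used it, no adjustment could separate route from country.

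The cost is small: a change of wording and somewhat more analysis. Route must be identifiable in the data anyway for the planned comparison of routes. The downside is lower precision for the US in the sensitivity analysis, more so the larger the panel's share.
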